### Blinding

The nature of this trial prevents the blinding of both the treating clinicians and patients. Both clinicians and patients will be exposed to the allocation via a) what modality they receive their physiotherapy service, and b) health-related data from activity trackers. Outcome measures will be collected by a blinded assessor. Randomisation will only occur after initial baseline assessment. Patients will always be approached by an unblinded clinical team prior to reassessment to mitigate risk of unblinding of the assessor (e.g. removing wristbands for the assessment).

### Sample size

The minimum clinically important difference (MCID) for the CFQ-R has been previously calculated for people with CF who are medically stable (using distribution/Smallest Error Measurement method) as 6.1 (A. L. [24]). Standard deviation on CFQ-R improvement (treatment burden) has been previously reported as 8.6 [25]. A power of 0.9 and an alpha value of 0.025 has been chosen for this trial. Using this information, sample size for each group has been calculated to be 42 participants per group [26]. To allow for patient dropout, a total of 55 participants per group will be recruited.

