### Study design

This is a single centre, prospective parallel randomised controlled non-inferiority trial with a 1:1 allocation across two treatment arms: Usual OPS and CyFiT OPS. Children receiving Usual OPS will serve as the control group for the trial.

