#### Primary outcome measure

##### Cystic fibrosis questionnaire – Revised (CFQ-R)

The CFQ-R is a valid and reliable quality of life measure for children with CF from 6 years of age (A. L. [18]). The score is positively correlated with pulmonary function in adolescents with CF [19]. It includes nine quality of life domains: physical (8 items), role limitation, vitality (5 items), emotional (5 items), social (6 items), body image (3 items), eating disturbances (3 items), treatment burden (3 items), and health perceptions (3 items); as well as three symptom-based scales: weight (1 item), respiratory (6 items), digestion (3 items). All items are scored on a 4-point Likert Scale (1 = Very true/Always to 4 = Not at all true/Never). Scores for each domain will be analysed individually.

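### The 90% power is not supported for the primary outcome as defined: the 6.1 has no named CFQ-R scale, the SD of 8.6 belongs to treatment burden alone, and every scale is analysed individually

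*Protocol article*

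**What the plan says.** The Study design section describes a "single centre, prospective parallel randomised controlled non-inferiority trial with a 1:1 allocation across two treatment arms".

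The Sample size section gives the inputs. The difference is introduced as "The minimum clinically important difference (MCID) for the CFQ-R has been previously calculated for people with CF who are medically stable", with its derivation and value given as "using distribution/Smallest Error Measurement method) as 6.1". No CFQ-R scale is attached to that value. The variability is scale-specific: "Standard deviation on CFQ-R improvement (treatment burden) has been previously reported as 8.6". The error rates follow: "A power of 0.9 and an alpha value of 0.025 has been chosen for this trial". The result is 42 per group, raised to 55 per group for dropout.

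The section on the CFQ-R as primary outcome lists nine quality-of-life domains and three symptom scales. Treatment burden is one of the shorter ones: "treatment burden (3 items", and "All items are scored on a 4-point Likert Scale". On analysis it says: "Scores for each domain will be analysed individually". It does not mark treatment burden, or any other scale, as the one on which non-inferiority is judged.

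**The concern.** A power statement holds for one endpoint, with a margin and an SD measured on that endpoint. Here the 6.1, which acts as the margin in the calculation, is not tied to a scale. The SD is tied to a single three-item scale. The primary outcome covers all the scales. The link between margin, SD and endpoint is therefore missing, and a single 90% is offered for all of them.

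This matters because power in a non-inferiority trial is sensitive to the SD. If the scale that decides the trial varies more than 8.6, the confidence interval widens. The trial may then fail to exclude a 6.1-point deficit even when the two services are equivalent. With 42 completers per group the calculation leaves nothing in hand against that.

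**Working it through.** **Inputs.** Margin 6.1, SD of change 8.6, alpha 0.025, power 0.90, 42 per group (55 recruited), all from Sample size; 1:1 allocation from Study design. Sidedness is not stated.

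**Step 1: reproduce the plan's figure.** With a true difference of zero,

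n per group = 2 × (1.960 + 1.282)² × (SD / margin)² = 2 × 10.507 × (8.6 / 6.1)² = 2 × 10.507 × 1.9876 = 41.77, rounded up to 42.

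One-sided 0.025 therefore gives the published number. Two-sided 0.025 would give 50 and one-sided 0.05 would give 35. The arithmetic is correct, so the question is about the inputs.

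**Step 2: how much slack there is.** Solving the same formula for the SD,

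largest SD for 90% power = 6.1 / (3.2415 × √(2/n)).

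- n = 42: 8.62, against the 8.6 assumed.
- n = 55: 9.87.

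Since 55 is the dropout allowance (13/55 = 23.6%), 42 is the planned number of completers. The value at 55 is an upper bound.

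**Step 3: power over a range of SDs.** The documents give no SD for any other CFQ-R scale, so the values above 8.6 are assumptions. Power is the probability that a noncentral t variable, with 2n − 2 degrees of freedom and noncentrality 6.1 / (SD × √(2/n)), exceeds the 97.5th percentile of the central t distribution.

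| SD of change | Power, 42 per group | Power, 55 per group |
|---|---|---|
| 8.6 (plan) | 90% (89.5%) | 96% |
| 10 | 79% | 89% |
| 12 | 63% | 75% |
| 15 | 45% | 56% |

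**Step 4: a conditional check on 8.6.** The article says that 6.1 came from a distribution or measurement-error method. Suppose that 6.1 is exactly one standard error of measurement (SEM), that it belongs to the same scale as the 8.6, and that errors at the two visits are independent. Measurement error alone then gives a change-score SD of √2 × 6.1 = 8.63. That is already the whole of the assumed SD (2 × 6.1² / 8.6² = 1.006), which leaves no room for real differences between children in how they change. If 6.1 belongs to another scale, the check falls away, but then margin and SD have been taken from different scales.

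**Step 5: what baseline adjustment would recover.** With correlation r between baseline and follow-up and equal variances, adjusting for baseline multiplies the variance of the change-score comparison by (1 + r)/2. At an assumed r = 0.5 the factor is 0.75, so an SD of 12 becomes 12 × √0.75 = 10.4. Power at 42 per group rises from 63% to 76%.

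**The case against.** The strongest reply is that nothing is miscalculated. The 42 reproduces exactly, the 8.6 is cited to a published source that cannot be inspected here, and every larger SD above is an assumption. With all 55 per group evaluable, 90% power survives to an SD of about 9.9, and baseline adjustment would recover more. All of this stands. It limits the conclusion but does not supply the missing link between the margin, the SD and the primary scale.

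A reader might go further in four ways that the documents do not support.

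- **That the trial will not have its stated power.** The true SD is not given, so this cannot be shown. The supportable statement is that 90% is not justified for the primary outcome as defined.
- **That the article's own figures prove 8.6 to be pure measurement error.** The 8.63 in Step 4 needs 6.1 to be one SEM of treatment burden, and the article gives neither the multiplier nor the scale. One cannot object that the scale is unnamed and also assume that it is known.
- **That three four-point items make 8.6 impossibly small.** On a 0–100 rescaling, which the article does not state, one response step is 100/9 = 11.1 points, larger than both 6.1 and 8.6. But an SD limits spread around the mean, not movement: if every child improved by one step, the SD of change would be zero. Even with zero mean change, the constraint is p₁ + 4p₂ = (8.6/11.11)² = 0.599, where p₁ and p₂ are the proportions moving one and two steps. Up to 0.599/4, or 15%, could move two steps. A margin below one step is not an error either, because group means are not confined to steps.
- **That an inconclusive result is the likely outcome.** At 42 per group, power falls below one half only above an SD of about 14, and nothing in the documents establishes an SD that large.

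**Conclusion.** The concern holds as an unsupported sample-size assumption, not as an arithmetic error. The 90% applies to at most one of twelve individually analysed scales, and only if 6.1 is a valid margin for treatment burden. At 42 completers per group there is no tolerance for a larger SD; at 55 the tolerance extends to about 9.9. Over assumed SDs of 10 to 15, power runs from 79% down to 45% at 42 per group and from 89% down to 56% at 55. These figures rest on a one-sided 0.025 test, a true difference of zero and an unadjusted comparison of change scores. The match between √2 × 6.1 and 8.6 is a reason to check the source of both numbers and should carry no more weight than that.

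**What to change.** 1. Name one CFQ-R scale and one time point as primary, and treat the other scales as secondary.
2. Take both the margin and the SD of change from that scale, and say so in Sample size. If treatment burden is chosen, show that 6.1 applies to it. If another scale is chosen, replace the 8.6.
3. Replace the single 90% with power over a plausible SD range at 42 and 55 per group, as in the table above, and state that alpha is one-sided.
4. Analyse the primary scale adjusted for its baseline value, which the plan already collects.

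A check of the pooled SD, blind to arm, from the baseline and 6-month data would be useful but is optional.

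The cost is a recalculation and a less favourable stated power. None of these steps requires added enrolment or new data collection.

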### Data analysis

All statistical analyses will be performed using SPSS 24 (IBM Corp., Armonk, NY, USA). Data will be analysed on an intention-to-treat basis. Generalised linear models will be used to determine any differences between repeated outcome measures across Usual OPS and CyFiT OPS. Missing data will be handled using predictive mean matching imputations using five observed cases for each missing value and a total of five imputed data sets will be pooled as the final result [27]. Statistical significance will be set at *p* < 0.05.

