We aim to investigate the efficacy of various modes of telehealth at our clinic. In this trial, we have developed a multi-modal telehealth-based OPS specific for children with CF. This trial seeks to answer the following question: Can CyFiT OPS offer a non-inferior health outcome and quality of life compared to Usual OPS for children with CF? If proven to be effective, the new model of healthcare delivery will be integrated into our existing services as an alternative option for families particularly those living far away from the hospital CF Centre.

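### The trial is declared non-inferiority, but its only stated between-group analysis tests for any difference, with no declared margin or decision rule

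*Protocol article*

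**What the plan says.** The Study design section of the protocol article calls this a "single centre, prospective parallel randomised controlled non-inferiority trial with a 1:1 allocation across two treatment arms", and the abstract says the same. The Background section puts the research question as "Can CyFiT OPS offer a non-inferior health outcome and quality of life compared to Usual OPS for children with CF".

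The Sample size section gives the minimum clinically important difference ("using distribution/Smallest Error Measurement method) as 6.1") and an SD for one domain: "Standard deviation on CFQ-R improvement (treatment burden) has been previously reported as 8.6". It continues: "A power of 0.9 and an alpha value of 0.025 has been chosen for this trial". The result is 42 per group, raised to 55 for dropout. The 6.1 is not called a margin, and the sidedness of alpha is not stated.

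The Data analysis section has one sentence on comparing the arms: "Generalised linear models will be used to determine any differences between repeated outcome measures across Usual OPS and CyFiT OPS". It then says "Statistical significance will be set at *p* < 0.05", again without sidedness. The 6.1 does not reappear, and there is no confidence-interval criterion.

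The section on the primary outcome has each CFQ-R domain analysed on its own. The Study duration section sets assessments at baseline and at 6, 12 and 18 months. Neither a primary domain nor a primary time point is named.

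**The concern.** The design and the stated analysis address different null hypotheses. Non-inferiority requires rejecting the hypothesis that CyFiT OPS is worse by at least a margin. The stated analysis tests whether the difference is zero. Failing to reject zero is not evidence that a loss is small. It becomes more likely as data become noisier or fewer, which is the wrong incentive for a trial that hopes to find no loss.

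This goes beyond detail that an article would leave to a statistical analysis plan. The article does state an analysis, and that analysis does not match the declared hypothesis. The margin is also a design quantity that belongs with the sample size, which the article does give. The primary conclusion is at stake, because the article foresees bringing the new model into routine service if the result is favourable.

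**Working it through.** **Inputs.** From Sample size: difference 6.1, SD 8.6, alpha 0.025, power 0.9, 42 per group before dropout and 55 recruited. From Data analysis: significance level 0.05. Allocation is 1:1. Normal quantiles are 1.960 (one-sided 0.025) and 1.2816 (power 0.9). Differences are CyFiT minus Usual. Higher is taken as better, in line with the article's remark that the score correlates positively with lung function.

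**1. The protocol's own figure.** With 6.1 as margin and zero true difference:

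n = 2 × (1.960 + 1.2816)² × 8.6² / 6.1² = 41.8, so 42 per group.

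The stated figure is reproduced. A two-sided 0.05 superiority calculation for a difference of 6.1 has the same formula and also gives 42, so the sample size does not show which hypothesis was meant. Two-sided 0.025 would give 49.3, so 50, and one-sided 0.05 would give 35.

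**2. Standard error,** SE = 8.6 × √(2/n):
- 42 per group: 1.877
- 55 per group, if nobody were lost: 1.640

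**3. Where the two criteria fall.** Non-inferiority at 6.1 needs an estimate above −6.1 + 1.960 × SE. A two-sided 0.05 test is non-significant on the unfavourable side down to −1.960 × SE.
- 42 per group: −2.42 against −3.68
- 55 per group: −2.89 against −3.21

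Estimates between the two values show no significant difference yet fail non-inferiority. The zone is 1.26 points wide at 42 per group and about 0.33 at 55.

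**4. Error if non-significance were taken as non-inferiority.** With a true deficit of 6.1:

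P(non-significant) = Φ(1.960 − 6.1/SE) − Φ(−1.960 − 6.1/SE); the second term is negligible at SD 8.6.
- 42 per group: 6.1/1.877 = 3.250, and Φ(−1.290) = 9.8%
- 55 per group: 6.1/1.640 = 3.720, and Φ(−1.760) = 3.9%

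A non-inferiority test with a 6.1 margin would wrongly succeed with probability Φ(−1.960) = 2.5% at either size.

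**5. Sensitivity to SD.** The 8.6 belongs to one domain (treatment burden), while every domain is to be analysed. The protocol gives no other SD, so the larger values below are assumptions.

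| SD | 42 per group | 55 per group |
|---|---|---|
| 8.6 (protocol) | 9.8% | 3.9% |
| 12 (assumed) | 36% | 24% |
| 15 (assumed) | 54% | 43% |
| 20 (assumed) | 71% | 64% |

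**6. Effect of declaring 6.1 as the margin.** Power at zero true difference = Φ(6.1/SE − 1.960), which is Φ(1.290) = 90.2% at 42 per group and Φ(1.760) = 96.1% at 55. The sample size does not change.

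**The case against.** The strongest defence is that the pieces of a non-inferiority analysis are almost all present. The design is declared, 6.1 with alpha 0.025 and 90% power reproduces 42 as a non-inferiority calculation, and the planned model yields an estimate and a 95% CI that can be set against a margin. The Data analysis section is a short paragraph covering all outcomes, and a fuller decision rule may exist elsewhere. This defence limits how far the criticism can go. It does not remove it, because the sentence that is there states the wrong hypothesis and the 6.1 is never declared a margin.

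Several stronger readings are tempting but not supported:
- *The 0.025 and 0.05 levels contradict each other.* A reader might infer this, and then a doubled error rate. One-sided 0.025 and two-sided 0.05 are the same threshold and correspond to the same 95% CI. A doubling would need the 0.05 to be one-sided, which nothing says. What stands is that neither section states sidedness.
- *The trial cannot answer its question.* That holds only for the analysis as worded. The same model would serve with a declared margin and rule.
- *The sponsor will read p > 0.05 as non-inferiority.* No section says so. The wording leaves that reading open but does not commit to it.
- *The harm is larger than 9.8%.* A true 3-point deficit would be non-significant 64% of the time at 42 per group, but such a deficit lies inside a 6.1 margin, so calling it non-inferior would not be an error. The shares of 36% and above rest on assumed SDs. On the protocol's own SD the figures are 9.8% and 3.9%.

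**Conclusion.** The point holds: a declared non-inferiority trial states a difference test as its only between-group analysis, and neither a margin nor a decision rule is declared. On the protocol's SD, treating non-significance as non-inferiority would pass a treatment worse by the full 6.1 points in 9.8% of trials at 42 per group, or 3.9% at 55, where a non-inferiority test allows 2.5%. The excess is modest at SD 8.6 and grows quickly if a domain is more variable.

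These figures assume that 6.1 is the margin, a simple two-group comparison of means with normal quantiles, and no gain or loss of precision from repeated measures or imputation. The 55 per group figure is the best case with no dropout. The logical mismatch depends on none of these. It bears on the primary conclusion and should be corrected before results are seen, since a margin chosen afterwards would not be credible.

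**What to change.** **Sample size section.** Declare the non-inferiority margin and justify it clinically. If the margin is 6.1, explain why a loss of up to a full minimum clinically important difference is acceptable. State that alpha 0.025 is one-sided.

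**Data analysis section.** Name the primary CFQ-R domain and time point; without them a rule on the CFQ-R difference is undefined, since domains are analysed separately at three post-baseline visits. Then state that non-inferiority is concluded only if the lower limit of the two-sided 95% CI for CyFiT minus Usual (higher = better), from the planned model, lies above minus the margin. Keep two-sided p < 0.05 for secondary difference tests, and say that non-significance there will not be read as non-inferiority. This matters because the research question also covers health outcome.

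**Cost.** No new data are needed, and with a 6.1 margin and SD 8.6 no more patients: n stays at 42 per group. The wording is short, but choosing and justifying the margin, domain and time point is a real decision. A different margin, or a domain with a different SD, means recomputing the sample size.

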### Recruitment process

Participants of this study will be recruited from the CHQ-HHS CF service, Queensland, Australia. This service is provided via inpatient and outpatient services at (i) the CHQ-HHS LCCH, (ii) regional Queensland Health hospitals.

Children will be identified by the study coordinator who is a senior physiotherapist will review each patient attending the CF clinic, OPS, or hospital ward daily. The inclusion and exclusion criteria will be used to determine the eligibility for each child. All eligible children will be approached by the treating physiotherapist. If families express interest in the trial, a member of the research team will provide written information and seek consent/assent as appropriate. If the parents agree for their child to proceed with the study, informed written consent will be gained from the parent and assent from the child.

Once informed written consent is gained, baseline assessment will be collected by the blinded research assessor, which includes seven elements, the:, (i) Cystic Fibrosis Questionnaire-Revised (CFQ-R) (A. [13]), (ii) Modified Shuttle Test (MST25) [14], (iii) Measure of Processes of Care (MPOC) Questionnaire (S. M. [15]), (iv) Children’s Assessment of Participation and Enjoyment (CAPE), (v) Preferences for Activities of Children (PAC) (G. A. [16]), (vi) lung function (i.e. FEV_1_, FVC, FEV_1_/FVC, FEF_25–75%_)[17], and (vii) anthropometric data: height (cm), weight (kg) and age (y).

Once baseline assessment has been scheduled, a physiotherapist will randomise the child to one of the two treatment arms by opening a sealed allocation envelope in front of the child. The physiotherapist will then discuss with the families the requirements relevant to their allocation (e.g. how to access the telehealth system).

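### As worded, the model for repeated CFQ-R scores names neither within-child correlation nor baseline, so it fits neither the data nor the SD of change used for sizing

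*Protocol article*

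**What the plan says.** All places are in the protocol article.

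- **Data analysis:** "Generalised linear models will be used to determine any differences between repeated outcome measures" across the two arms. The section also fixes the software version, intention to treat, the imputation method and a significance level of 0.05. It says nothing about how scores from the same child are related, or whether baseline enters the model.
- **Study duration:** outcomes are taken at baseline, 6, 12 and 18 months. The 12-month visit ends the intervention, and all children are back on usual care by 18 months.
- **Recruitment process:** "baseline assessment will be collected by the blinded research assessor", and the CFQ-R is one of its elements, so every randomised child should have a baseline score.
- **Sample size:** the minimum important difference is 6.1. "Standard deviation on CFQ-R improvement (treatment burden) has been previously reported as 8.6". "A power of 0.9 and an alpha value of 0.025 has been chosen for this trial". From these, "sample size for each group has been calculated to be 42 participants per group", raised to 55 for dropout.

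**The concern.** A generalised linear model in its ordinary form assumes independent observations. Up to four CFQ-R scores from one child are not independent. The usual tools for such data are a mixed model or generalised estimating equations (GEE), and the section names neither.

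There is also a mismatch with the sizing. The SD of 8.6 describes improvement, that is, change from baseline. The stated analysis compares the outcome scores themselves, with no change score and no baseline covariate. The quantity that was powered is therefore not visibly the quantity to be analysed.

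At stake are the width of the confidence interval on which the non-inferiority conclusion rests and the assurance of the planned 90% power. An analysis plan that carried this sentence over literally would inherit both problems.

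**Working it through.** **Inputs from the article.** Difference 6.1, SD of change 8.6, alpha 0.025, power 0.90, 42 per group (55 recruited). Sidedness of alpha is not stated.

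**Assumptions.** The difference of 6.1 serves as the margin and the true difference is zero. Variances are equal across visits and any two visits have the same correlation ρ. The article gives no ρ, so a range of 0.3 to 0.8 is shown. Normal approximations are used throughout.

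**Reproducing the stated size.** n = 2(1.960 + 1.282)² × 8.6² / 6.1² = 41.8, so 42 per group, as stated (alpha one-sided 0.025). The standard error is 8.6√(2/42) = 1.877 and power is Φ(6.1/1.877 − 1.960) = 0.902. The sample size is internally correct for an analysis with SD 8.6.

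**(a) Arm effect averaged over three follow-up visits, independence assumed.** The model's SE is 1/√(1+2ρ) of the true SE. One-sided error is Φ(−1.960/√(1+2ρ)).

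| ρ | model SE / true SE | one-sided error |
|---|---|---|
| 0.3 | 0.79 | 0.061 |
| 0.5 | 0.71 | 0.083 |
| 0.7 | 0.65 | 0.103 |

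**(b) Change (group-by-time) contrast, independence assumed.** The model's SE is 1/√(1−ρ) times the true SE. Power at 42 per arm is Φ(3.250 − 1.960/√(1−ρ)), where 3.250 = 6.1/1.877.

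| ρ | model SE / true SE | power |
|---|---|---|
| 0.3 | 1.20 | 0.818 |
| 0.5 | 1.41 | 0.684 |
| 0.7 | 1.83 | 0.371 |

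**(c) Single-visit contrast.** The two arms hold different children, so under equal variances the independence SE is correct. What changes is the SD. Without baseline it is the raw SD, 8.6/√(2(1−ρ)). With baseline as covariate it is raw SD × √(1−ρ²), which simplifies to 8.6√((1+ρ)/2) and so never exceeds 8.6.

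| ρ | raw SD | unadjusted power, 42 | unadjusted power, 55 | adjusted SD | adjusted power, 42 |
|---|---|---|---|---|---|
| 0.3 | 7.27 | 0.970 | 0.993 | 6.93 | 0.981 |
| 0.5 | 8.60 | 0.902 | 0.961 | 7.45 | 0.964 |
| 0.6 | 9.62 | 0.828 | 0.914 | 7.69 | 0.953 |
| 0.7 | 11.10 | 0.712 | 0.822 | 7.93 | 0.941 |
| 0.8 | 13.60 | 0.538 | 0.653 | 8.16 | 0.929 |

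At ρ = 0.5 the raw SD equals the SD of change, so unadjusted power is the planned 0.902. Above that it falls. With baseline adjustment, 90% power needs 28, 32, 34, 36 and 38 per arm at the five correlations, always fewer than 42.

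**The case against.** The strongest reply is that silence is not a decision. This is a condensed article, and covariance structure and covariates are commonly left to the full protocol or analysis plan, neither of which is shown. The sentence itself calls the outcomes repeated, which fits a correlated-data extension. That stands: the article excludes neither within-child correlation nor baseline. It stands less firmly than usual because the same paragraph goes down to the software version and the number of imputed data sets, while the model class it names does not suit the data it names.

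Three stronger conclusions are tempting, and the document supports none of them.

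- *The standard errors are wrong in general.* They are not. The error is downward in (a), upward in (b) and absent in (c).
- *Non-inferiority will be declared too often.* That follows only for an averaged-over-visits arm effect. The article does not specify that contrast, and it would include the 18-month visit, taken after all children revert to usual care.
- *The 90% power is not delivered.* The 42 per group reproduces with power 0.902. A shortfall needs either an unadjusted single-visit comparison with a correlation above about 0.5, or an independence analysis of change. If all 55 per arm were retained, the unadjusted comparison would still have 0.914 at a correlation of 0.6.

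Nor can the harms be added together, since they belong to different contrasts. It is also fair that an unadjusted comparison in a randomised trial is valid. Baseline adjustment is a matter of precision, and the choice between a mixed model and GEE is open.

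**Conclusion.** The point holds as a matter of wording that should be tightened. Taken literally, the named model class fits neither the repeated measurements nor the SD of change on which the trial was sized.

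The size of the consequence is conditional. It rests on a literal independence model for the averaged and change contrasts, on an unadjusted analysis for the single-visit contrast, and throughout on assumed correlations, equal variances and a common correlation between visits. On those terms, one-sided error for an averaged contrast is about 6% to 10% for correlations of 0.3 to 0.7. Power for a change contrast is 0.82 down to 0.37 over the same range. Power for an unadjusted single-visit contrast runs from 0.97 to 0.54 for correlations of 0.3 to 0.8. The planned 90% is therefore not assured, which is weaker than saying it is missed.

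The part that does not depend on which correlation is true is the remedy: across the whole range tried, a baseline-adjusted model with within-child covariance meets or exceeds the planned power at 42 per arm.

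**What to change.** Replace the model sentence with wording such as: *CFQ-R scores at 6, 12 and 18 months will be analysed with a model that accounts for correlation within child (a linear mixed model for repeated measures, or generalised estimating equations), with arm, visit, arm-by-visit interaction and baseline score as covariate. The arm contrast at 12 months, the end of the intervention, will be reported with its 95% confidence interval.*

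This ties the analysis to the sizing, because the adjusted SD is at most the 8.6 assumed. If the analysis plan already says this, it is enough to make the two documents agree. The cost is wording only: the baseline score is already collected, the named software can fit the model, and no extra visits or children are needed.

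### Five imputed data sets are too few for the dropout the sample size allows: a modest, avoidable loss of power and of repeatability

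*Protocol article*

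**What the plan says.** The Data analysis section of the protocol article commits to a specific imputation procedure: predictive mean matching, with five donors per missing score. It also settles how many completed sets there will be: "a total of five imputed data sets will be pooled as the final result". The analysis principle is fixed as well: "Data will be analysed on an intention-to-treat basis". The number of sets is therefore a stated choice for the main analysis, and the section gives no rule for raising it if many outcomes are missing.

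The Sample size section takes a minimum clinically important difference of 6.1 and an SD of 8.6 and states that "A power of 0.9 and an alpha value of 0.025 has been chosen for this trial". It arrives at 42 per group and adds: "To allow for patient dropout, a total of 55 participants per group will be recruited". It gives no dropout percentage. It calls 6.1 an important difference and never names it as a non-inferiority margin.

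**The concern.** Multiple imputation replaces each missing score with random draws, so the pooled result carries simulation noise that shrinks as the number of sets grows. Five sets are often defended because the point estimate is then about 95% as efficient as with unlimited sets. That defence does not cover the confidence limit. With five sets the between-imputation variance rests on four degrees of freedom, so both the standard error and the t multiplier are unstable, and the interval is wider on average.

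A non-inferiority conclusion normally rests on one confidence limit. If a material share of outcomes is imputed, two runs of the same analysis on the same data could put that limit on different sides of the margin. The trial would also give back part of the power that the 13 extra children per arm were recruited to protect.

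**Working it through.** **Inputs.** From Sample size: difference 6.1, SD 8.6, alpha 0.025, power 0.9, 42 needed and 55 recruited per group. From Data analysis: five donors and m = 5 sets. Assumed: 6.1 serves as the margin, the true difference is 0 unless stated, and the correlation rho between earlier data and the missing score ranges from 0 to 0.7, because the article gives no value.

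**Reproducing the plan's figure.** n = 2 × (1.960 + 1.282)² × 8.6² / 6.1² = 41.8, so 42 per group, as stated. This treats 0.025 as one-sided. The implied allowance is (55 − 42)/55 = 13/55 = 23.6%.

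**Closed form, no useful predictor.** With unlimited imputations the variance of the difference is that of 42 per arm: 8.6² × 2/42 = 3.522 (SE 1.877). Taking 23.6% of it as between-imputation variance gives B = 0.8325 and W = 2.689. Rubin's total is T = W + (1 + 1/m)B.

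- m = 5: T = 2.689 + 1.2 × 0.8325 = 3.688; SE 1.921; Barnard-Rubin df 32.0; t = 2.037; power = Φ(6.1/1.921 − 2.037) = 87.3%.
- m = 50: T = 2.689 + 1.02 × 0.8325 = 3.538; SE 1.881; df 73.6; t = 1.993; power = Φ(6.1/1.881 − 1.993) = 89.4%.

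The loss is about 2.2 points. This understates it slightly, because B is held at its average when in practice it is estimated from five values. The simulation SD of the pooled difference alone is √(B/m): 0.408 with five sets and 0.129 with 50.

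**Simulation.** 55 per arm, predictive mean matching with five donors, Rubin pooling with Barnard-Rubin df. The reference SD of 8.6 was read either as the SD left after using earlier data (residual) or as the whole SD (total).

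| Missing per arm | SD 8.6 read as | rho | Power, 5 sets | Power, 50 sets | Loss (points) |
|---|---|---|---|---|---|
| 13 | residual | 0 | 86.3% | 89.7% | 3.4 |
| 13 | residual | 0.3 | 86.0 to 87.4% | 89.0 to 89.6% | 2.3 to 2.9 |
| 13 | total | 0.3 | 89.0% | 91.4% | 2.4 |
| 13 | total | 0.6 | 97.0% | 98.1% | 1.1 |
| 6 | total | 0.5 | 97.6% | 97.9% | 0.3 |

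The ranges in the second row come from separate runs; the 2.9 is a paired comparison on 9,948 trials with a standard error of 0.17. The 3.4 is the extreme, with no predictor at all; the same runs with Rubin's older df give 87.4% and 90.1%, a loss of 2.8. For comparison, analysing the 42 completers per arm without imputation has power of about 89.5%, so under weak prediction five sets do slightly worse than not imputing.

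**Seed dependence, 13 missing per arm, weak prediction.** The lower limit varies between seeds with an SD of about 0.6 points with five sets (0.58 to 0.68 across runs with residual SD 8.6) and about 0.15 with 50. Two seeds disagree on non-inferiority in 6.5% of trials at a true difference of 0, and in 11.7 to 13.8% at −2. With 50 sets the figures are 2.1 to 3.0% and 3.9 to 4.4%. Disagreement with five sets at a true difference of 0 falls to about 3.8% at rho 0.5 and 1% at rho 0.7.

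**Type I error.** In simulation, false non-inferiority was about the same with 5 and with 50 sets.

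**The case against.** Much of the case on the other side stands, and it limits the size of the point.

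- **The dropout rate.** A reader might take 24% as the planned dropout. The article gives no rate; 13/55 is the largest loss that the recruitment target can absorb. With about half that, the cost falls below 1 point.
- **Predictive data.** The Study duration section schedules outcomes at baseline, 6, 12 and 18 months, and the Withdrawal section keeps data collected before withdrawal. Many children who leave will have an earlier score to impute from, which reduces both the power loss and the seed noise.
- **The decision rule.** Comparing a lower limit with 6.1 is an assumption. The Data analysis section speaks of differences at p < 0.05, and the primary outcome section analyses each questionnaire domain separately. Every power and disagreement figure here depends on that assumed rule.
- **Validity.** A reader might infer that five sets make the test invalid. They do not: Rubin's rules allow for a small number of sets, and the price is a wider interval, which works against a false claim of non-inferiority. The seed SD of 0.6 is also about a third of the sampling SE (0.6/1.88 = 0.32), so the verdict changes only in trials already near the margin, and 50 sets do not remove this entirely.
- **Treatment arm in the imputation model.** A reader might also infer that arm is left out, which would pull the groups together. The article lists no imputation predictors at all, and that detail commonly belongs to an analysis plan that is not shown. There is no basis for that criticism. The same applies to the absence of a stated seed, which is not a fault in itself.

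What survives is that five is a fixed choice, it is low for the missingness the design allows, and nothing is gained by keeping it.

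**Conclusion.** The point holds as a modest refinement. If the whole allowance of 13 per arm is used and earlier data predict the missing score weakly, five sets instead of 50 cost about 2 to 3 points of power, and the lower limit moves between seeds with an SD of about 0.6 points rather than about 0.15. With half the dropout or strongly predictive earlier visits, the power cost is about 0.3 to 1 point. These sizes rest on an assumed margin of 6.1, a single primary comparison, an SD of 8.6 and assumed correlations. They concern only the number of sets, not whether the missing-data assumption is sound. The analysis is not invalid as written, but a borderline result could depend on an arbitrary seed.

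**What to change.** In the Data analysis section, replace five imputed data sets with at least 50, and record the random seed before the imputation is run. The five donors per missing value can stay as they are. In runs using normal imputation with no predictor and 13 missing per arm, power was 86.7% with 5 sets, 89.0% with 20, 89.4% with 50 and 89.7% with 100, so 20 sets recover most of the loss and 50 nearly all of it. A recorded seed makes the run repeatable, but only the larger number of sets makes the answer less dependent on which seed was chosen. The change is one sentence and minutes of computing, with no extra participants, visits or data.
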